#### Other outcomes

(1) Molecular mechanism: Surfactant protein D (SP-D) and N-terminal pro-brain natriuretic peptide (NT-proBNP). Serum SP-D levels are considered to be a disease marker value for human lung diseases, including interstitial lung diseases (ILDs), COPD, and asthma [27]. Serum BNP levels may [28] help identify right heart failure or pump thrombosis/malfunction. Many clinical trials have shown that Tai Chi training effectively reduces the level of brain natriuretic peptide in patients with chronic heart failure [29] and myocardial infarction.

(2) Berg balance scale: Disturbance of balance is the most common cause of disability in stroke patients. The Berg balance scale has been widely used to evaluate poststroke patients’ abilities [30]. The scale consists of 14 items, each of which is divided into 5 grades from 0 to 4, with a full score of 56. Higher scores indicate better balance.

### Participant timeline {13}

The participant timeline is shown in Table 2.

**Table 2 Tab2:**
[figure not shown]
Example template of recommended content for the schedule of enrollment, interventions, and assessments

### Sample size {14}

Sample size estimation in this trial is based on the expected improvement of VO_2Peak_ in 12 weeks of Tai Chi training in patients with heart failure [31]. After 12 weeks of intervention, the VO_2Peak_ of the aerobic exercise group and Tai Chi group was respectively 13.0 ± 4 ml/kg/min and 15.2±6 ml/kg/min. We set *α* = 0.05, *β* = 0.10. The sample size will be estimated according to the estimation formula:
$$ {n}_1={n}_2=2{\left[\frac{\left({t}_{2a}+{t}_{2\beta}\right)\;s}{\delta}\right]}^2 $$

It is estimated that a sample size of 94 participants per group will be required. Considering a 20% dropout and exit rate, we will recruit 226 participants, with 113 participants in each group.

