### Trial design {8}

This study will be a multicenter, single blind (assessor and statistician), 19-week, randomized parallel control group trial. Patients will be allocated in a 1:1 ratio into the control group or Tai Chi group.

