## Statistical methods

### Statistical methods for primary and secondary outcomes {20a}

Statistical analysis will be performed by statisticians who come from the third term using SPSS 20.0 software for Windows. Categorical variables will be expressed in terms of frequency or percentage, and continuous variables will be expressed in terms of mean and standard deviation. Primary and secondary outcome data collected after 13 weeks and 19 weeks will be compared with baseline data, respectively. For normally distributed variables, a *t* test will be used for statistical comparisons between groups. If it is nonnormal, then a nonparametric test is used. *P* values less than 0.05 will be considered statistically significant. To verify that the results are consistent, the primary outcome (change in VO_2Peak_ between baseline and 19 weeks) will be compared between the two groups using intention-to-treat (ITT) and per-protocol subject analysis (PPS). The Pearson correlation or Spearman correlation measures the correlation between two variables.

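### The 94 per group follows from the printed formula only as a one-sided 5% calculation; read as a two-sided test, the plan's own inputs give about 84% power (82% after its dropout), not 90%

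*Protocol article*

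**What the plan says.** All inputs are in the Protocol article.

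- **Sample size {14}.** The error rates are "We set *α* = 0.05, *β* = 0.10". The VO2peak values after 12 weeks, for aerobic exercise and Tai Chi in patients with heart failure, are "respectively 13.0 ± 4 ml/kg/min and 15.2±6 ml/kg/min". The printed formula is n = 2[(t(2α) + t(2β))·s/δ]². The result is "It is estimated that a sample size of 94 participants per group will be required", followed by "Considering a 20% dropout and exit rate, we will recruit 226 participants, with 113 participants in each group".
- **Trial design {8}.** Allocation is 1:1.
- **Statistical methods {20a}.** The test is given as "For normally distributed variables, a *t* test will be used for statistical comparisons between groups", with a nonparametric test otherwise, and P "values less than 0.05 will be considered statistically significant". The primary outcome is described there as the change in VO2peak from baseline to 19 weeks.

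Neither section says in words whether the test is one-sided or two-sided.

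**The concern.** The sample size section and the analysis section appear to rest on different tests. The doubled subscript on α makes 0.05 a one-sided level in the sample size formula. The analysis section gives a plain t test at P < 0.05, which a reader takes as two-sided.

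If the test is two-sided, the false-negative rate is larger than the stated 0.10. If it is one-sided, the success rule allows 5% error in the favourable direction instead of the usual 2.5%, and only a subscript discloses it. Leaving this open until results are known would let a P value that passes one-sided but not two-sided be reported either way.

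**Working it through.** **Inputs.** δ = 15.2 − 13.0 = 2.2. Pooled variance s² = (4² + 6²)/2 = 26, so s = 5.10. α = 0.05, β = 0.10, allocation 1:1.

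**Reproducing the plan's 94.** I read t(2α) and t(2β) as two-tailed table values, that is, one-sided 5% and 10% quantiles.

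- Normal quantiles: 2 × (1.645 + 1.282)² × 26/4.84 = 92.0.
- t with 100 df: 2 × (1.660 + 1.290)² × 26/4.84 = 93.5, which rounds up to 94.
- t with the design's own 186 df: 92.8, so 93.

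One-sided power at 94 per group is 90.4% (noncentral t), which agrees with β = 0.10.

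**The same inputs, two-sided.** 2 × (1.960 + 1.282)² × 26/4.84 = 112.9, so 113 per group. By the exact t test, 113 gives 89.8% and 114 gives 90.0%.

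**Could another SD explain 94 two-sided at 90% power?** It would need s = 4.65. The average of the two SDs (5.0) gives 109, an SD of 4 gives 70 and an SD of 6 gives 157. None fits.

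**Effect of the dropout step.** 94 × 1.2 = 112.8, so 113. If 20% are lost, 113 × 0.8 = 90.4, so about 90 remain rather than 94. Keeping 94 would take 94/0.8 = 117.5, so 118 per group.

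**Power at the plan's own numbers** (exact t, δ = 2.2, s = 5.10):

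| Evaluable per group | One-sided 5% | Two-sided 5% |
|---|---|---|
| 94 | 90.4% | 83.7% |
| 90 | 89.2% | 82.1% |
| 113 (no loss) | 94.4% | 89.8% |

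Two-sided β is therefore 0.16 to 0.18.

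**The planned change score.** The SD of 5.10 describes values at follow-up, not changes. With equal variances at both times and baseline/follow-up correlation r, the SD of the change is 5.10 × √(2(1 − r)). The residual SD for an analysis adjusted for baseline (ANCOVA) is 5.10 × √(1 − r²). The document gives no r, so the values below are assumptions. Two-sided 5%, 90 per group:

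| Assumed r | t test on change | ANCOVA |
|---|---|---|
| 0.3 | 68% | 85% |
| 0.5 | 82% | 91% |
| 0.7 | 96% | 98% |

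At r = 0.5 the change score has the same SD as the follow-up value, so its power is the same.

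**The case against.** **The strongest reply** is that the sample size section contains no error: the formula is printed, 94 follows from it, and one-sided power at 94 is 90.4%. The objective is also directional (Tai Chi improves fitness), and the analysis section never says two-sided. Much of this stands. A reader might infer that 94 is a miscalculation, and the documents do not support that. The figure is consistent with its own formula, and the two-sided reading of the analysis is convention rather than stated text. What survives is that a directional hypothesis does not declare a one-sided test and the analysis section declares none. The level of the primary test is thus left to a subscript.

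**Second reply:** 113 per group are recruited, which gives 89.8% two-sided. That requires no loss at all, while the section itself assumes 20%.

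**Third reply:** 84% is not the power of the planned analysis, because the primary comparison is of change to 19 weeks. This is correct. A reader might take 84% as the trial's true power, but it is only what the section's own inputs give for a comparison of follow-up values. With 94 per group and r = 0.6, a t test on change would have 91% two-sided; with r = 0.3 it would have 70%.

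**Fourth reply:** the drop from 84% to 82% has nothing to do with sidedness. That is also correct. It comes from multiplying by 1.2 instead of dividing by 0.8, and is a separate, smaller slip.

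**Conclusion.** The point holds in a conditional form. If the primary test is two-sided at 5%, the stated β of 0.10 is not delivered on the section's own inputs. Power is about 84% with 94 per group and about 82% with the 90 that remain after the assumed loss; 90% would need 113 to 114 evaluable per group. If the test is one-sided, 94 is right for 90% power, but the rule needs to be declared.

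The figures assume a difference of 2.2, a common SD of 5.10 and a comparison of follow-up values. For the change score they move with a correlation that the document does not give.

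A reader might conclude that the trial is too small to be worthwhile or must recruit more. The figures do not show that: on the section's own inputs, two-sided power stays above 80% even after dropout. This is a should-fix matter, with a stated figure and an undeclared rule to bring into line.

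**What to change.** 1. State in both Sample size {14} and Statistical methods {20a} that the primary VO2peak test is two-sided at 5%, and replace t(2α) with the two-sided quantile.
2. Keep 226 patients. Restate the power as about 84% with 94 evaluable per group and about 82% with the 90 expected after 20% loss. Note that this uses the SD of follow-up values, and that 94 × 1.2 does not preserve 94 after a 20% loss.
3. If a 90% claim is to be kept, make baseline-adjusted ANCOVA the primary analysis and give the power as a range over assumed correlations (with 90 per group: about 85% at 0.3, 91% at 0.5, 98% at 0.7). At 0.3 the claim would still fail, so a single assumed value is not enough.

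Steps 1 and 2 cost some rewording in two sections, a less favourable power statement and no extra patients. Step 3 is optional and changes the planned test. All of it should be settled before the allocation is uncovered, so that sidedness cannot be chosen in the light of the result.

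### The 20% dropout allowance was added as 20% of the required number, so 113 recruited per group leaves about 90 evaluable, not the 94 the protocol requires

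*Protocol article*

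**What the plan says.** All the figures are in the Sample size section (item 14) of the protocol article.

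- Error rates: "We set *α* = 0.05, *β* = 0.10".
- Expected VO2peak after 12 weeks in the aerobic exercise and Tai Chi groups, taken from a study in heart failure: "respectively 13.0 ± 4 ml/kg/min and 15.2±6 ml/kg/min".
- Requirement: "It is estimated that a sample size of 94 participants per group will be required".
- Allowance for loss and recruitment target: "Considering a 20% dropout and exit rate, we will recruit 226 participants, with 113 participants in each group".

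The Trial design section fixes equal allocation: "Patients will be allocated in a 1:1 ratio into the control group or Tai Chi group". The Methods part of the abstract repeats the total of 226 at 1:1. The article does not write out the formula that takes 94 to 113, and it gives no other dropout rate or inflation rule.

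**The concern.** An allowance for dropout has one purpose: after the expected loss, the number left should be the number the power calculation asked for. The section gives the requirement, the loss rate and the recruitment target, so the reader can test this directly, and the test fails. At the stated loss rate, the stated target leaves fewer participants than the stated requirement.

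What is at stake is the power claim. The protocol sets β at 0.10 and presents 94 per group as the number that achieves it. If the trial recruits and loses participants exactly as planned, it will analyse fewer than that. The fault is independent of how the 94 was derived, and of whether α is read as one-sided or two-sided.

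**Working it through.** **Inputs, all from the Sample size section:** required n = 94 per group; dropout d = 0.20; recruited n = 113 per group (226 in total); means 13.0 and 15.2, so difference δ = 2.2; SDs 4 and 6; α = 0.05; β = 0.10.

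**1. Where the 94 comes from.** Pooled SD = √((4² + 6²)/2) = √26 = 5.10. The normal-approximation formula is n = 2[(z_α + z_β)·SD/δ]².

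- One-sided α: 2[(1.645 + 1.282) × 5.10/2.2]² ≈ 92.0, so 93 after rounding up. This is within two patients of 94.
- Two-sided α: 2[(1.960 + 1.282) × 5.10/2.2]² ≈ 112.9, so 113. This does not give 94.

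The 94 therefore fits a one-sided test at 0.05. That is a separate issue; from here 94 is taken as given. The two-sided requirement of 113 equals the recruitment target only by coincidence, because the protocol presents 113 as the number after the dropout allowance.

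**2. Reproducing the 113.**

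- n × (1 + d) = 94 × 1.20 = 112.8, so 113. Exact match.
- n / (1 − d) = 94 / 0.80 = 117.5, so 118. No match.

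**3. What 113 delivers.**

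| Quantity | Calculation | Result |
|---|---|---|
| Remaining per group at 20% loss | 113 × 0.80 | 90.4, about 90 |
| Remaining in total | 226 × 0.80 | 180.8, against 188 required |
| Shortfall per group | 94 − 90 | 4 |
| Largest loss that still leaves 94 | 1 − 94/113 | 16.8% |
| Recruits per group needed for 94 at 20% loss | 94/0.80 = 117.5 | 118 |
| Recruits in total | 2 × 118 | 236 (10 above 226) |

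**4. Effect on power.** Two-sample t test, noncentral t with 2n − 2 degrees of freedom and noncentrality δ/(SD·√(2/n)), with δ = 2.2 and SD = 5.10. The noncentrality is 2.96 at n = 94 and 2.89 at n = 90.

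| Evaluable per group | One-sided 0.05 | Two-sided 0.05 |
|---|---|---|
| 94 | 90.4% | 83.7% |
| 90 | 89.2% | 82.1% |
| Loss due to the dropout step | about 1.1 points | about 1.6 points |

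Only the last row belongs to this point. The gap between the two columns comes from the sidedness of α.

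**The case against.** The strongest objection is size. A loss of 1.1 to 1.6 points of power is well within the uncertainty of the planning inputs, which are whole-number SDs from heart failure patients. With a common SD of 5 in place of 5.10, the one-sided normal-approximation requirement falls to 89 per group, which the 90 remaining would meet. That is correct, and it means the slip by itself does not put the trial at risk. It does not make the three published figures agree.

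A second objection is that multiplying by 1.2 is a common habit and that the protocol never says in words that 94 will remain. But the text calls the 20% a dropout and exit rate, not a margin on the required number, and an allowance that does not protect the 94 has no purpose.

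A third is that an intention-to-treat comparison is planned, so a participant who drops out is not automatically lost to analysis. This has some force: the shortfall applies to participants who provide no outcome. However, the section on non-adherence and missing data says only that missing-data patterns will be examined and names no way of recovering lost VO2peak values. The protocol's own inflation of 94 also treats dropout as a loss of usable participants.

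Finally, if α is corrected to two-sided, the requirement itself changes and the figures of 94, 118 and 236 are superseded. That is a reason to correct both points together, not to leave this one.

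**Conclusion.** The error stands. A target of 113 per group does not deliver 94 evaluable per group at 20% loss; it delivers about 90. The shortfall is 4 evaluable participants per group (8 in total), or 10 recruits against 236. The power cost is about 1.1 points one-sided, which moves the plan from just above its 90% target to just below it, or about 1.6 points two-sided.

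This rests on three assumptions: that 20% means a share of those recruited, that those participants contribute no VO2peak outcome, and that the protocol's means and SDs apply. The head counts need only the first two. The finding is a small but definite inconsistency that should be corrected; it is not a threat to the design.

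**What to change.** Keep 226 and correct the sentence. State that with 20% loss about 90 per group are expected to be evaluable, and give the power for 90 per group together with the sidedness it assumes: 89.2% for a one-sided test at 0.05, or 82.1% for a two-sided test. This sentence should be settled together with the sidedness of α, because that decides which power figure belongs in it.

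An alternative is to say that 113 per group preserves 94 for losses up to 16.8%. This is accurate, but it fits the loss rate to the sample size, so it should not hide that the expected loss was 20%. What should not remain is 94 required and 20% dropout beside 113.

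The cost is one sentence and a slightly less favourable stated power. No change to recruitment, conduct or analysis is needed. If the sponsor prefers to keep both the 94 and the 20%, the consistent target is 118 per group, 236 in total.

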### Recruitment {15}

The patients will be recruited from the Xi Yuan Hospital, Beijing Da Xing District of Integrated Traditional Chinese and Western Medicine, Hebei Cang Zhou Hospital of Integrated Traditional Chinese and Western Medicine, Fujian University of Chinese Medicine, Henan Provincial People’s Hospital, The Third People’s Hospital of Zhengzhou, and Henan Provincial Hospital of TCM.

## Assignment of interventions: allocation

### Sequence generation {16a}

Participants will be randomly assigned to the control group or Tai Chi group (1:1) via block randomization at baseline using a central stochastic system.

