### Concealment mechanism {16b}

Allocation is not concealed and will be revealed to both the participants and the researcher upon randomization.

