### Implementation {16c}

Each hospital is equipped with a random staff. The account and password of the random staff are given to enter the random system (http://121.229.17.89:9080/IWRS/). Patients will receive a unique random number from random staff.

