## Assignment of interventions: blinding

### Who will be blinded {17a}

In this study, it will be impossible to blind the participants and Tai Chi coaches. To minimize bias, study personnel, such as researchers who perform relevant tests and outcome evaluators, will not have permission of a central stochastic system. Group A will be used to identify the control group, and group B will be used to identify the Tai Chi group, thus blinding the statisticians and outcome evaluators.

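### The concealment section says allocation is not concealed: it confuses concealment before enrolment with open-label disclosure afterwards and conflicts with the central, account-restricted randomisation system

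*Protocol article*

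**What the plan says.** All of the following is in the protocol article.

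- The method of assignment is given under Sequence generation {16a}, which reads as follows: "Participants will be randomly assigned to the control group or Tai Chi group (1:1) via block randomization at baseline using a central stochastic system". Neither a block length nor a stratification factor is given.
- Concealment mechanism {16b}, in full: "Allocation is not concealed and will be revealed to both the participants and the researcher upon randomization". Which researcher is meant is not said.
- Implementation {16c}: "Each hospital is equipped with a random staff". This person enters a web randomisation system with an account and password. "Patients will receive a unique random number from random staff".
- Who will be blinded {17a}: "In this study, it will be impossible to blind the participants and Tai Chi coaches". It adds that "study personnel, such as researchers who perform relevant tests and outcome evaluators, will not have permission of a central stochastic system". The physicians who recruit and consent patients are not named in that bar.
- Who will take informed consent {26a}: a lead physician judges eligibility, and a research physician takes consent after at least two weeks of reflection.
- Study setting {9} and Recruitment {15} list seven institutions. Sample size {14} plans for 226 patients: "we will recruit 226 participants, with 113 participants in each group".

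**The concern.** Concealment and blinding protect against different things. Concealment acts before a patient is entered: whoever decides on eligibility, consent and timing must not know, or be able to work out, which arm comes next. Blinding acts after assignment. An open trial cannot blind its participants, but it can and should conceal.

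Section {16b} is the place to say how the next assignment is hidden, and it says that it is not. Because the trial is open, coaches, participants and a researcher know the earlier assignments at their site. With 1:1 blocks, earlier assignments can carry information about later ones.

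Selection at entry would matter here. Patients may enter from 2 weeks to 6 months after stroke, so they may differ in how much they would recover without any exercise programme. Some exclusions need judgement, such as severe liver or kidney dysfunction, or a mental disorder that would prevent completion. If the mix of patients differed between arms because someone anticipated the assignment, the changes in VO2peak and SF-36 would differ without a treatment effect. Blinded assessment and an intention-to-treat analysis would not remove that difference.

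**Working it through.** **1. The sections side by side.** {16a} and {16c} describe a central system with restricted accounts, operated by a dedicated role at each hospital. Such a system can hold the sequence and release one assignment at a time. {17a} relies on the same restriction to keep testers and outcome evaluators unaware. {16b} then says that allocation is not concealed. Its second half, about disclosure on randomisation, describes what happens after assignment. The likeliest reading is that the first half was meant as open label. As written, however, the section contradicts the system described around it and leaves no stated safeguard before enrolment.

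**2. Why the size of the bias cannot be given.** The protocol states no figure to reproduce. Predictability depends on two settings that the article does not give: block length, and whether blocks are kept within hospital. The figures below are assumptions that show the range.

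Inputs from the protocol: 226 patients, seven sites (226/7 = about 32 per site), 1:1 ratio.

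For a fixed block of 2m within hospital, with the length known to the observer:

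- share of assignments known with certainty = 1/(m + 1)
- best-guess success rate = [m + 2^(2m−1)/C(2m, m) − 1/2] / (2m)

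For blocks of 4 (m = 2), the certain share is 1/3 and the success rate is (2 + 8/6 − 0.5)/4 = 0.708.

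| Assumed setting | Known with certainty | Best guess correct |
|---|---|---|
| Fixed 2, within hospital | 50% | 75% |
| Fixed 4, within hospital | 33% | 71% |
| Fixed 6, within hospital | 25% | 68% |
| Fixed 8, within hospital | 20% | 67% |
| Random 4/6/8, within hospital (simulated, 32 per site) | about 2% | about 68% |
| One list for seven sites, each site seeing only its own assignments (simulated) | not calculated | about 51% |

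**3. What steering could do, in units of g.** Suppose a recruiter always bets on the arm that is behind at the site. The recruiter enrols a patient whose expected change is higher by g when Tai Chi is guessed, lower by g when control is guessed, and does nothing when the arms are level. With success rate p, the between-arm shift is 2(2p − 1)g:

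- fixed blocks of 4 within hospital: 2(2 × 0.708 − 1)g = 0.83g
- random 4/6/8 within hospital (p = 0.675): 2(2 × 0.675 − 1)g = 0.70g
- one shared list (p = 0.51): 2(2 × 0.51 − 1)g = 0.04g

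No figure in the protocol gives g, so these shifts cannot be turned into ml/kg/min.

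**4. What the comparison implies for a remedy.** Random block lengths nearly remove certainty (33% to about 2%) but lower the success rate only from about 71% to 68%. If the system now runs one shared list, adding stratification by hospital would raise the success rate from about 51% to about 68%, and the shift from 0.04g to 0.70g.

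**The case against.** The strongest reply is that {16b} is loose wording and nothing more. It says that allocation is disclosed on randomisation, which points to disclosure after entry. A separate role operates the system, and eligibility and consent sit with other named roles. Many entry criteria are numeric (Berg score, MOCA score, blood pressure, heart rate, age). At least two weeks pass between the eligibility judgement and consent, so a tally kept at screening may be out of date at assignment. Delay is also limited, because entry closes six months after onset. A condensed article need not publish block lengths, and withholding them is sound practice.

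Most of this stands, and it limits the point. A reader might infer that blocks are run hospital by hospital and that recruiters can foresee assignments. The protocol does not support this. {16a} calls the system central and names no stratification, {16c} only places a login holder at each hospital, and no section says that the block length is fixed, is known to staff, or that an assignment is visible before entry. A reader might also convert step 3 into a share of the 2.2 ml/kg/min planned difference (15.2 − 13.0 in {14}). That would need within-hospital blocks, a known length, consistent steering in one direction across sites, and an invented g.

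The reply does not rescue the sentence itself. It is a stated rule under the concealment heading, and it denies the safeguard that the heading asks for. A fuller protocol could add detail, but this sentence would still need correcting.

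**Conclusion.** The point holds as a defect in what {16b} states. The section says that allocation is not concealed, treats concealment as if it were blinding, and conflicts with the restricted central system in {16a} and {16c}. Taken literally in an open, blocked 1:1 trial, it would leave enrolment open to selection bias. That is a risk, not an established consequence.

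The size is not determinable from the protocol. Foreseeability runs from near chance (about 51%) with one shared list to 67% to 75% with fixed blocks of 8 down to 2 kept within hospital and a known length. If the system already conceals properly, only the text is wrong. If staff follow the text, a basic protection of a randomised trial is missing. Correction is worthwhile in either case because it costs so little.

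**What to change.** 1. Replace the {16b} sentence with wording such as: *The sequence is held in the central system and is concealed from recruiting physicians, randomisation staff and patients. The system releases an assignment only after consent, eligibility and baseline tests have been recorded and the patient has been irrevocably registered. Participants and coaches learn the allocation only after release.*
2. In {17a}, extend the bar on system access to the physicians who recruit and consent patients.
3. State that block lengths are withheld from site staff. The lengths themselves need not be published.
4. Check how the system is set. If, and only if, it already runs blocks within hospital at a fixed length, vary the lengths at random for the remaining patients and report the change. This sharply cuts assignments known with certainty but reduces best-guess success only modestly, so it supplements items 1 to 3 and does not replace them.
5. Do not introduce stratification by hospital as a concealment measure. If the list is now shared, that would make assignments easier to guess.

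The cost is a short amendment to {16b} and {17a} and a check of the existing system's settings. No extra patients, staff or visits are needed. If lengths of 4, 6 and 8 were used under item 4, the arms within a site could differ by at most 4 patients, half of the largest block.
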